#### Secondary Outcome Analysis

Hospital LOS will be analyzed similarly using *t* tests or linear regression, with Cox regression as a secondary analysis. Although LOS data are likely to be nonnormally distributed, the *t* test and linear regression models are considered robust due to the sample size (n>30 per group), which satisfies the conditions of the central limit theorem.

HRQOL at 1 and 6 months will be assessed using linear mixed-effects models to account for repeated measures, and binary outcomes (eg, ICU admission and in-hospital mortality) will be compared using logistic regression. Biomarkers will be analyzed as change from baseline with adjustment for time from randomization to follow-up sampling. Linear regression and mixed-effects models incorporating time as a covariate will be used, with sensitivity analyses restricted to samples collected within a predefined time window.

Baseline differences between groups in clinical and demographic variables will be assessed using *t* tests, Wilcoxon rank-sum tests, or chi-square or Fisher exact tests as appropriate. Missing data will be addressed using multiple imputation, and additional sensitivity analyses will be performed in subgroups, such as patients with moderate to severe pneumonia (CURB-65 score≥2).

Statistical significance for all outcomes will be determined using a 2-sided type I error rate of α=.05. All analyses will be performed using Stata (version 19.0; StataCorp).

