## Introduction

### Background

Community-acquired pneumonia (CAP) is an acute infection of the pulmonary parenchyma that occurs outside the hospital setting and remains a major cause of hospitalization, morbidity, and mortality worldwide. Lower respiratory tract infections accounted for approximately 2.6 million deaths worldwide in 2019, ranking among the leading causes of death [1]. Population-based CAP studies from high-income countries report hospitalization rates of approximately 25 per 10,000 adults annually, with 20% to 25% of patients requiring intensive care unit (ICU) admission [2]. Mortality remains substantial, particularly among older adults and those with multimorbidity and frailty [3].

Recent Australian data highlight the persistent burden of CAP. In a large multicenter cohort of patients hospitalized with non–COVID-19 CAP, in-hospital and 30-day mortality rates were 7.8% and 16.9%, respectively, rising to 17.6% among those requiring ICU admission [4]. Despite advances in antimicrobial therapy and supportive care, outcomes have remained largely unchanged, underscoring the need for safe and effective adjunctive therapies to improve recovery and reduce complications.

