### Data Collection and Follow-Up

Clinical data will be collected daily during hospitalization. Follow-up assessments will be conducted at 30 days and 6 months after randomization via telephone interview. Data will be recorded using secure electronic case report forms. The schedule of enrollment, interventions, and outcome assessments is summarized in Table 1.

**Table 1 table1:** Schedule of enrollment, interventions, and assessments for the Vitamin C in Community-Acquired Pneumonia trial.

	Screening and baseline	Day 0—randomization	Days 1-7—hospital phase	Day 30—follow-up	Month 6—follow-up
Eligibility assessment	✓				
Informed consent	✓				
Randomization		✓			
Vitamin C or placebo administration		✓	✓	✓	
Clinical observations (vital signs)	✓	✓	✓^a^		
CAP^b^ symptom assessment	✓		✓	✓	
Early clinical response assessment			✓^c^		
Inflammatory biomarkers (CRP^d^ and PCT^e^)	✓		✓^f^		
Hospital outcomes (ICU^g^ admission, ventilation, and vasopressor use)			✓		
Length of stay			✓		
Adverse event monitoring		✓	✓	✓	✓
Hospital readmission				✓	
Health-related quality of life (EQ-5D-5L)				✓	✓
Mortality assessment			✓	✓	✓

^a^Daily during hospitalization (days 1-7).

^b^CAP: community-acquired pneumonia.

^c^Assessed on days 3-5.

^d^CRP: C-reactive protein.

^e^PCT: procalcitonin.

^f^Measured on day 7 or at discharge (whichever occurs first).

^g^ICU: intensive care unit.

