#### Primary Outcome Analysis

The primary outcome, time to clinical stabilization, will be analyzed using a Cox proportional hazard regression model with treatment group as the primary exposure. Results will be reported as hazard ratios with 95% CIs accounting for censoring. The proportional hazard assumption will be assessed using Schoenfeld residuals and log-log survival plots.

The primary Cox model will be adjusted for the following prespecified baseline covariates selected a priori based on clinical relevance: age, sex, baseline pneumonia severity (confusion, uremia, respiratory rate, blood pressure, and age ≥65 years [CURB-65] score), baseline C-reactive protein concentration, and key comorbidities (eg, chronic cardiovascular, respiratory, or metabolic conditions). These covariates were selected to account for potential confounding effects of multimorbidity on clinical recovery. Randomization is stratified by pneumonia severity to ensure balance between groups across this critical prognostic variable.

As a sensitivity analysis, time to clinical stabilization will also be assessed using restricted mean survival time over a clinically relevant time horizon, providing an absolute measure of treatment effect that does not rely on the proportional hazard assumption.

An additional sensitivity analysis will be performed using an independent-sample *t* test (2-sided) or linear regression depending on the distribution of the outcome. The linear regression model will allow for adjustment for the same prespecified covariates, and results will be reported as mean differences with 95% CIs.

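### The main analysis of hospital length of stay compares raw days, so an early in-hospital death counts as a short stay

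*Protocol article*

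**What the plan says.** **Length of stay.** In the Protocol article, Secondary Outcome Analysis, LOS is compared by t "tests or linear regression, with Cox regression as a secondary analysis". The section concedes that LOS will probably not be normally distributed and answers that both methods still serve: "linear regression models are considered robust due to the sample size (n>30 per group), which satisfies the conditions of the central limit theorem". It gives no rule for a stay that ends in death, in either the main or the Cox analysis. All outcomes are tested at a two-sided 5% level.

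**Deaths are expected.** Background reports that in an Australian cohort "in-hospital and 30-day mortality rates were 7.8% and 16.9%, respectively". Sample Size Calculation counts mortality within the 20% attrition allowance, and Secondary Outcome Analysis names in-hospital mortality among the binary outcomes.

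**Time to stabilization.** Primary Outcome Analysis states: "The primary outcome, time to clinical stabilization, will be analyzed using a Cox proportional hazard regression model with treatment group as the primary exposure". It adds: "Results will be reported as hazard ratios with 95% CIs accounting for censoring". Restricted mean survival time (RMST) is the first sensitivity analysis. Last comes a further sensitivity analysis on the days scale, by a t "test (2-sided) or linear regression depending on the distribution of the outcome".

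**Observation.** Footnote a to Table 1 describes the vital-sign schedule as "Daily during hospitalization (days 1-7". The text above the table promises daily clinical data throughout the hospital stay, with no upper day.

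**The concern.** A mean of raw days treats every end of stay alike. Someone who dies on day 2 contributes two days, as does someone who recovers and goes home on day 2. The first is the worst outcome in the trial and the second one of the best.

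Study Aim and Hypotheses predicts both a shorter stay (hypothesis 2) and lower mortality (hypothesis 4). On raw days these pull against each other: deaths averted count against hypothesis 2, and excess early deaths count toward it. The result will be read, since Consumer Engagement reports quick discharge as the patients' second priority.

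The central limit theorem says that a sample mean is close to normal in large samples. It does not make that mean the right quantity when some of the times were cut short by death.

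A related but smaller problem affects the additional mean-difference analysis of time to stabilization. A t test needs a completed time for each participant, and a censored participant has none.

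**Working it through.** **The plan's own figure.** The protocol gives no planning figure for LOS. Its sample size is a comparison of two means: a difference of 1.1 days, SD 1.95, 80% power and two-sided α of .05. The normal approximation gives n per arm = 2 × (1.96 + 0.84)² × 1.95² / 1.1² ≈ 49.3, so 50. The t-based version gives 50.3, so 51 per arm and 102 in total, as stated. The planned 62 per arm corresponds to 51 × 1.2 = 61.2, rounded up.

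**Expected deaths.** 62 × 0.078 = 4.8 per arm; 124 × 0.078 = 9.7 in total.

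**Artefact in mean LOS.** Suppose treatment has no effect on the stay of those discharged alive. Let m be their mean stay in both arms, d the mean day of death, and q the in-hospital mortality. The mean raw stay in an arm is (1 − q)m + qd. The difference, vitamin C minus placebo, is then

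−(q_T − q_C) × (m − d).

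Inputs:
- q_C = 0.078 (Background).
- Mortality ratio 0.51, the point estimate of the CAP-specific review in Study Justification (95% CI 0.24 to 1.09). Ratios of 1.5 and 2 are assumptions for the opposite direction.
- m = 4.7 days, the placebo mean in Sample Size Calculation. There, time to stabilization is treated as a proxy for discharge, so using it as a mean stay is an assumption. m = 8 is a further assumption.
- d is assumed.

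| m (days) | Mortality ratio | q_T − q_C | d (day) | Artefact (days) |
|---|---|---|---|---|
| 4.7 | 0.51 | −0.038 | 1 to 3 | +0.14 to +0.07 |
| 4.7 | 1.5 | +0.039 | 1 to 3 | −0.14 to −0.07 |
| 4.7 | 2 | +0.078 | 1 to 3 | −0.29 to −0.13 |
| 8 | 1.5 | +0.039 | 2 to 4 | −0.23 to −0.16 |
| 8 | 2 | +0.078 | 2 to 4 | −0.47 to −0.31 |

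First row, d = 1: 0.038 × (4.7 − 1) = 0.14. Last row, d = 2: 0.078 × (8 − 2) = 0.47. A positive value means that the vitamin C arm looks worse because fewer of its patients died. With equal mortality the artefact is zero.

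**Scale.** With the planning SD of 1.95 and 62 per arm, the standard error of a difference in means is 1.95 × √(2/62) = 0.35 day. On the 4.7-day mean, every entry is below one standard error. The SD for LOS is not given and may differ.

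**Does the secondary Cox analysis repair this?** Not as written. If the event is end of stay for any reason, death still counts as an early success. If death is censored like a loss to follow-up, the deceased are treated as people who would later have gone home. The text does not say which applies.

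**Time to stabilization.** The Cox model and RMST can both take censored times. The t test and linear regression cannot: such a time must be dropped, entered as if it were the event time, or imputed. Choosing between the two methods by the distribution of the outcome does not settle this.

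**The case against.** The strongest reply is that the LOS artefact is small, needs a mortality difference, and concerns one of many secondary outcomes. Mortality is also reported separately, so a stay shortened by deaths would be noticed. All of that stands and limits the grade of the point. It does not rescue the method, which the protocol fixes and argues for on a ground that misses the problem. That detail could sit in an unseen analysis plan is a fair answer to silence, but less so to a stated choice.

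Several stronger readings are tempting and are not supported:

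- **That the primary result is compromised.** It rests on a Cox model that accounts for censoring, followed by RMST. The t test is only an additional sensitivity analysis.
- **That censored times will be scored as recoveries or dropped, or that multiple imputation will supply stabilization times for the dead.** The article says none of these. They are alternative possibilities.
- **That intention to treat is breached.** Statistical Methods makes that commitment for the primary analysis, not for a sensitivity t test.
- **That observation ends at day 7.** Assuming a strict cut-off and gamma-distributed times with the planning means and SDs, 5.7% and 12.8% would be unresolved at day 7. The 1.10-day difference would become 1.00 if these were scored as day 7, or 0.84 if dropped. But the text promises daily collection throughout the stay, and the same Table 1 column holds LOS and ICU admission, which cannot sensibly stop at day 7.
- **That halved mortality shifts LOS by 0.2 to 0.4 day.** This needs each averted death to add 5 to 10 days of stay, and the document gives no source for that. Nor can the shift be judged against 1.1 days, which is the stabilization target; no LOS target is stated.

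**Conclusion.** The point holds for length of stay. Followed as written, the main analysis lets an early in-hospital death count as a short stay, and the central limit argument does not meet this. With about 5 deaths expected per arm, the artefact is about 0.07 to 0.14 day if mortality is roughly halved on a 4.7-day mean, and up to about 0.5 day if mortality doubles on an assumed 8-day mean. These sizes rest on the cited cohort's mortality applying here, on the assumed mean stay and day of death, and on a mortality difference between arms. The direction needs only that difference and that deaths come earlier than a typical discharge.

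For time to stabilization only a lesser point holds: the additional t test or linear regression has no place for censored times and adds nothing that RMST does not give properly.

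**What to change.** 1. **LOS.** Replace the main analysis with either time to discharge alive, with in-hospital death as a competing event so that the deceased are never counted as discharged, or days alive and out of hospital to day 30. Report raw LOS descriptively, by survival status.
2. **Cox analysis of LOS.** If it is kept, state how death enters.
3. **Time to stabilization.** Delete the t test and linear regression. Let the planned RMST difference be the days-scale result, with participants who die counted as not stabilized up to the horizon.
4. **Table 1.** Reconcile footnote a with the text of Data Collection and Follow-Up, so that vital signs are captured until stabilization or discharge.

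Cost: analysis wording and one table footnote, with no change to sample size or treatment. Days alive and out of hospital also needs readmission dates, not just the fact of readmission. The downside is that LOS is no longer summarized by a simple mean difference. Recruitment is scheduled to start in 2026, and the change is best made before any outcome data are examined.

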### Sample Size Calculation

The sample size was based on a previous RCT [16], which reported that the mean time to clinical stabilization (used as a proxy for hospital discharge) in patients with CAP was 3.6 (SD 1.9) days in patients who were in the vitamin C group compared to 4.7 (SD 2.0) days in the placebo group. Using this effect size (1.1 days), a pooled SD of 1.95, a power of 80%, and a 2-sided α of .05, the required sample size is 102 participants (51 per group). To account for an anticipated 20% attrition rate due to loss to follow-up or mortality, we plan to recruit 124 participants (62 per group).

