### Randomization and Allocation Concealment

Randomization will be performed using a computer-generated sequence with variable block sizes and stratification by pneumonia severity. Allocation concealment will be ensured via a centralized pharmacy service responsible for dispensing sequentially numbered, identical study medications.

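### Randomization is stratified by severity, but the secondary analyses are not committed to that factor: length of stay may be compared by a plain t test, and the biomarker models name only time

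*Protocol article*

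**What the plan says.** The Randomization and Allocation Concealment section specifies "variable block sizes and stratification by pneumonia severity". The Primary Outcome Analysis section gives the reason: "Randomization is stratified by pneumonia severity to ensure balance between groups across this critical prognostic variable". The CURB-65 score is among the covariates of the primary Cox model, and the linear-regression sensitivity analysis of the primary outcome may carry the same list.

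The Secondary Outcome Analysis section sets out the following:

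- **Length of stay:** handled in like manner to the preceding section, by t test or linear regression, with Cox regression in second place.
- **Biomarkers:** change from baseline, adjusted for time from randomization to the follow-up sample. Time is the only covariate named.
- **Quality of life:** linear mixed-effects models, with no covariates named.
- **Binary endpoints:** "binary outcomes (eg, ICU admission and in-hospital mortality) will be compared using logistic regression", with no covariates listed or excluded.

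One significance rule covers everything: "Statistical significance for all outcomes will be determined using a 2-sided type I error rate of α=.05".

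**The concern.** Stratified randomization balances the arms on severity, so differences between strata contribute almost nothing to the true sampling variance of a treatment difference in means. An analysis that ignores the strata still counts that variation as noise. Its standard error is then larger than the design warrants, its actual type I error falls below the nominal level, and power is lost.

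The plan avoids this in its primary model but does not carry the principle through to the secondary outcomes. The t test for length of stay matters most, because it is a named method that cannot accommodate the factor, not a detail left open. Nor does the plan give a working rule for choosing between the t test and regression. The preceding section lets the distribution of the outcome decide, while the Secondary Outcome Analysis section calls both methods robust to non-normality on the same central-limit argument. An unadjusted and an adjusted analysis of length of stay are therefore both permitted.

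What is at stake is precision on secondary outcomes for which the protocol states no power.

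**Working it through.** **1. The plan's own figure.** The inputs, from Sample Size Calculation, are a difference of 1.1 days and "a pooled SD of 1.95, a power of 80%, and a 2-sided α of .05". The normal formula gives 2 × 1.95² × (1.96 + 0.84)² / 1.1² ≈ 49.3, so 50 per group. The t-based calculation gives 50.3, so 51 per group and 102 in total, as stated. The recruited 124 follows from 51 × 1.2 = 61.2, rounded up to 62 per group. These figures concern the primary outcome. No power or sample size is given for any secondary outcome.

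**2. Differences in means (length of stay, biomarker change).** Let R² be the share of outcome variance explained by the randomization strata. The protocol does not give it, so 5%, 10% and 20% are assumed. With 1:1 allocation within strata:

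- ratio of reported to true standard error = 1/√(1 − R²)
- true two-sided alpha = 2[1 − Φ(1.96/√(1 − R²))]
- power without the stratum, for a comparison with 80% power when adjusted = Φ(2.80 − 1.96/√(1 − R²))

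| R² | SE too wide by | True alpha | Power, adjusted → unadjusted |
|---|---|---|---|
| 0.05 | 2.6% | 4.4% | 80% → 79% |
| 0.10 | 5.4% | 3.9% | 80% → 77% |
| 0.20 | 11.8% | 2.8% | 80% → 73% |

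For R² = 0.10, for example, 1/√0.90 = 1.054, and 1.96 × 1.054 = 2.066, which gives alpha 3.9%.

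A second illustration borrows the primary outcome's inputs (51 per group, 1.1 days, SD 1.95). Adjusted against unadjusted power is 83.2% and 81.9% at R² = 0.05, 85.2% and 82.6% at 0.10, and 89.0% and 84.0% at 0.20. The losses are 1.3, 2.6 and 5.0 points. Across the two illustrations the loss is about 1 to 7 points.

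**3. Binary outcomes.** The formulas above do not apply to a log odds ratio, so this was simulated: 124 participants, two equal strata, 1:1 within strata, 6,000 replicates per scenario (non-converging fits dropped, at most 78 in any scenario). The control risks and the conditional odds ratio of 0.35 are assumptions.

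| Control risk, low/high severity | Mean reported SE of log OR, without → with stratum | Power, without → with stratum |
|---|---|---|
| 15% / 30% | 0.561 → 0.569 | 48.9% → 49.6% |
| 10% / 40% | 0.517 → 0.543 | 50.0% → 53.2% |
| 20% / 60% | 0.411 → 0.451 | 63.2% → 70.1% |

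Adding the stratum raises the reported standard error in every scenario. Power still rises, because the severity-conditional log odds ratio lies further from zero than the marginal one (in the third scenario the mean estimate moves from −0.932 to −1.095). The smallest gain, 0.7 points, is about the size of the Monte Carlo error of one rejection rate, √(0.5 × 0.5/6000) = 0.65 points.

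With no treatment effect, the model without the stratum rejected in 3.5% to 4.6% of replicates and the model with it in 4.9% to 5.0%. The unadjusted reported standard error exceeded the empirical SD in two scenarios (0.422 against 0.407; 0.370 against 0.339) and about equalled it in the third (0.439 against 0.440).

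**4. Sparseness.** At the 7.8% in-hospital mortality that the Introduction cites, 124 × 0.078 ≈ 10 deaths are expected, so a mortality model has little room for covariates.

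**The case against.** The strongest reply is that this turns silence into an error. No sentence says that the secondary models are unadjusted. Covariate lists for secondary models are commonly left to an analysis plan, and this is a condensed article. Length of stay is tied to the preceding section, whose linear regression can carry CURB-65, so one permitted route already contains the factor. The variance share is assumed, and the strata's cut points are not given. Any error is conservative, and the primary analysis already adjusts.

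Most of this stands, and it rules out two stronger readings. A reader might infer that the secondary analyses omit severity. The text supports only that they are not committed to it. A reader might also infer that intervals for ICU admission, ventilation, vasopressor use and mortality are too wide by the percentages above. Those percentages hold for differences in means only, and with logistic regression the adjusted interval for the log odds ratio is the wider one.

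What the reply does not answer is the t test. It is named as an acceptable analysis of length of stay, it cannot include the stratification factor, and nothing workable decides between it and regression. The biomarker sentence likewise specifies an adjustment and leaves severity out of it.

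**Conclusion.** The point holds at minor severity. For length of stay by t test, and for the biomarker models if time is their only covariate, the reported standard error would be 2.6% to 11.8% too wide, the true alpha 4.4% to 2.8%, and the power loss about 1 to 7 points. This rests on an assumed R² of 0.05 to 0.20 for the strata.

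For binary outcomes the covariates are simply unstated. Leaving severity out would cost some power (0.7 to 6.9 points in the assumed scenarios), not widen the log-odds-ratio interval.

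False positives do not become more likely, and the primary Cox analysis is untouched. That the stratification variable is CURB-65 is inferred from the Primary Outcome Analysis section; the randomization section says only pneumonia severity.

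**What to change.** In Secondary Outcome Analysis:

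- Replace the t test for length of stay by linear regression that includes the severity stratification factor. This also removes the open choice between methods.
- State that the other secondary models (biomarkers, quality of life, logistic) include the same factor.
- Where events are sparse, make the stratifier the only added covariate.

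The cost is a change of wording before recruitment. Severity is already recorded for randomization and for the primary model, so no new data are needed. The small downside is one extra parameter in sparse models, such as the one for in-hospital mortality.

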## Methods

### Study Design

This study is a single-center, double-blind, placebo-controlled, parallel-group randomized clinical trial designed in accordance with the SPIRIT (Standard Protocol Items: Recommendations for Interventional Trials) 2013 statement. Participants will be randomly allocated in a 1:1 ratio to receive either high-dose oral vitamin C (as sodium ascorbate) or a matching placebo in addition to standard care for CAP (Figure 1).

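### Significance tests of baseline differences between randomized arms are uninformative and should be replaced by description; the primary estimate is not affected

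*Protocol article*

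**What the plan says.** The Secondary Outcome Analysis section plans hypothesis tests on the baseline table: "Baseline differences between groups in clinical and demographic variables will be assessed using". The methods it then lists are the two-sample t test and, for other kinds of variable, "Wilcoxon rank-sum tests, or chi-square or Fisher exact tests as appropriate". It gives no purpose for them and no threshold of their own. The 5% level in the same section is stated for outcomes: "Statistical significance for all outcomes will be determined using a 2-sided type I error rate of α=.05".

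The allocation is sound. Study Design gives a 1:1 ratio, and Randomization and Allocation Concealment says: "Randomization will be performed using a computer-generated sequence with variable block sizes and stratification by pneumonia severity". Concealment is through a central pharmacy, and participants, clinicians, assessors and statisticians are blinded.

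Adjustment is treated separately. Under Primary Outcome Analysis: "The primary Cox model will be adjusted for the following prespecified baseline covariates selected a priori based on clinical relevance". The set is age, sex, CURB-65, baseline C-reactive protein and key comorbidities. The additional sensitivity analysis on the mean difference is a t test or a linear regression, and the regression may carry the same covariates. Length of stay is handled in a similar way, again with a t test as an option.

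**The concern.** A test of baseline balance asks whether a difference could be due to chance. After proper randomization it is due to chance, so the answer is known before the data are seen. Nor does the P value measure what matters to the treatment comparison, which is the size of an imbalance multiplied by the variable's link with the outcome.

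Such tests can mislead in two directions. A chance flag may be taken as a fault in the randomization. A non-significant result may be taken as balance on a variable where a moderate imbalance matters. The sentence also sits awkwardly beside the prespecified covariates, because a column of baseline P values has no use in a plan whose adjustment is already fixed.

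**Working it through.** **Inputs from the protocol.** 62 randomized per arm, outcome SD 1.95 days and planning effect 1.1 days (Sample Size Calculation); concealed 1:1 allocation stratified by severity (Study Design; Randomization and Allocation Concealment).

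**Assumed.** A 5% level for the baseline tests; the number of variables k, since no baseline table is listed; and the correlation between the test statistics.

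**1. The protocol's own figure.** Normal approximation: 2 × (1.960 + 0.842)² × 1.95² / 1.1² = 49.3, or 50 per arm. The t-based calculation gives 50.3, rounded up to 51 per arm, or 102. The stated figure reproduces, and dropping the baseline tests does not alter it.

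**2. Chance flags.** For k independent tests with true nulls, P(at least one P<.05) = 1 − 0.95^k. The correlated columns come from 200,000 simulated sets of equally correlated normal test statistics.

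| k | independent | correlation 0.2 | correlation 0.4 |
|---|---|---|---|
| 10 | 40% | 38% | 32% |
| 15 | 54% | 50% | 41% |
| 20 | 64% | 59% | 49% |
| 25 | 72% | 66% | 54% |

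The chance first passes one half at k = 14 if the tests are independent (1 − 0.95^14 = 51%; 49% at k = 13). The protocol mentions about 16 candidates: age, sex, CURB-65, C-reactive protein, procalcitonin, three comorbidity groups, frailty, Charlson index, five vital signs and a symptom score. For 16 independent variables the figure would be 56%, but several of these overlap, so the true value is lower.

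**3. What the tests pass over.** An observed difference is significant only if it exceeds t(.975; 122 df) × √(2/62) = 1.98 × 0.180 = 0.36 SD. A 0.30 SD imbalance gives t = 0.30 / 0.180 = 1.67, P = .097.

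**4. Why P is the wrong measure.** An imbalance of d SD in a variable correlated r with the outcome shifts an unadjusted mean difference by r × d × SD. With d = 0.30, SD = 1.95 and r assumed at 0.4 to 0.5, the shift is 0.23 to 0.29 day, or 21% to 27% of 1.1 days. This is the same whether or not a test is run. Adjustment for the variable deals with it; a test does not.

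**5. Gain from fixed adjustment of the mean difference.** If the covariates explain R² of the outcome variance, the standard error falls by a factor of about √(1 − R²). For an assumed R² of 0.2 to 0.3 this is 0.89 to 0.84, a reduction of 11% to 16%.

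**6. Limit of that adjustment.** Counting each of the three example comorbidity groups as one term, the set has seven terms, or eight with treatment. If the 7.8% in-hospital mortality cited in the Background applied here, 124 × 0.078 gives about 10 deaths, little more than one event per term. The full set is unsafe in that logistic model.

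**The case against.** The strongest reply is that nothing specified in the plan changes. That stands for the primary analysis: its covariates are prespecified and randomization is stratified by severity.

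A reader might infer that the baseline P values will select covariates for the less tightly fixed analyses. The protocol does not say so. It names the same prespecified set for the linear regression, and ties the choice between t test and regression to the distribution of the outcome. A power loss computed for adjustment guided by P<.05 would therefore describe a procedure that this plan does not contain.

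A reader might also infer that most trials of this kind would show a significant baseline difference. That needs about 14 or more independent variables. The protocol lists no baseline table, and its candidates overlap: CURB-65 contains age, respiratory rate and blood pressure, and the comorbidity groups overlap with the Charlson index. No significance threshold is stated for these tests either. How the report would word a flag or a non-significant result is not known.

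The tests could be defended as a check on the conduct of randomization. The protocol gives them no such purpose, and scattered P values at 5% are a poor check for it, given the chance flags shown above.

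What remains is that the tests are planned, their nulls are true by design, and description without P values is better at no cost.

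**Conclusion.** The point holds and is minor. The planned baseline tests carry no useful information under any assumption about the number of variables. The frequency of chance flags depends on assumptions: 40% for 10 independent variables and 54% for 15, falling to 32% and 41% at a correlation of 0.4. The 0.36 SD threshold needs only the 62 per arm and the assumed 5% level.

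The primary hazard ratio, its error rate and the sample size are unaffected. The only room for improvement in an estimate lies in the analyses where an unadjusted t test is still an option, namely length of stay and the mean-difference sensitivity analysis. There, committing to the prespecified covariates would improve precision, by an amount that depends on an R² the protocol does not give.

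**What to change.** - Replace the sentence on baseline tests with one stating that baseline characteristics will be summarized by arm (mean and SD, median and interquartile range, or number and percentage) without significance tests. Standardized differences may be added.
- State that the covariates of the primary model, including CURB-65 severity, will be used in the linear regressions for length of stay and for the mean-difference sensitivity analysis, in place of the optional unadjusted t test, whatever the baseline table shows.
- For sparse binary outcomes such as in-hospital death, prespecify a reduced set, for example the severity stratum only. The full set should not be extended to every model.

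The cost is a few sentences. Sample size, alpha and data collection stay as they are, and there is less to analyze. The change should be made before any comparison of outcomes by arm.
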